### Sampling strategy

Households will be selected using a hybrid sampling technique to obtain as random of a sample as is feasible. Because a truly random sample would be logistically infeasible due to expense and lack of a household-level sampling frame, a hybrid systematic and random sampling technique will be used. To accomplish this, a modified procedure based on the World Health Organization Expanded Programme of Immunization (EPI) method will be used [10,11]. First, each area will be split into 127 grid squares using Geographic Information System (GIS) technology. The center point of each grid cell will then be generated using GIS. This is the starting location for the enumerators for each day’s survey. GPS will be used to navigate to the precise starting location each morning.

After arrival at the center point, the spin-the-bottle technique will be used [10]. Each enumerator team will be supplied with a random direction by spinning a pen or bottle. On arrival to the center of the grid cell, they will travel in the given direction surveying houses along the line given by the direction.

As many of Lwala’s programs and outcomes of interest focus around maternal and child health, households with children under five years of age will be oversampled. At least five of seven surveys administered in each grid square will be administered to households with children under five years. If the enumerator reaches the end of the grid cell before surveying both seven total households and five households with a child under five years, they will walk along the edge of the grid to the closest corner to find more households.

This approach minimizes the biases of the traditional spin-the-bottle sampling method [12] by using the center of an arbitrary square in place of the center of a town or gathering area.

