### Survey instrument

The survey tool contains over 300 questions and is based on several different validated tools (Table 3). The full survey is available in the supplemental materials (S1 Appendix). The survey is designed to capture metrics across 13 public health modules in a reproducible manner. The estimated time to complete one interview is 45 minutes.

**Table 3 pone.0256555.t003:** Survey modules, key metrics, and sample sizes.

Survey Section	Question Sources	Key Metrics
Personal Demographics	Kenya Demographic and Health Survey [1]	Age Marital status
Household Information	Kenya Demographic and Health Survey [1]	Household census Birth history (child mortality) Total fertility rate
Economics	Kenya Demographic and Health Survey [1] Poverty Probability Index [13]	Poverty probability Multidimensional poverty index Income
Family Planning	Kenya Demographic and Health Survey [1] Condom Use Self-Efficacy Scale [14]	Contraceptive prevalence rate Unmet need for contraception
Child Health	Kenya Demographic and Health Survey [1]	Antenatal care visits Careseeking for childhood illness
Nutrition	WHO Infant and Young Child Feeding [15] Household Hunger Scale [16]	Ever breastfed Exclusive breastfeeding Minimum acceptable diet Household hunger
Vaccinations	Kenya Demographic and Health Survey [1]	Complete vaccination rate
HIV	Kenya Demographic and Health Survey [1] van Rie Stigma Scale [17–19]	HIV testing rate HIV stigma
Water and Sanitation	Kenya Demographic and Health Survey [1]	Drinking water source Previous sanitation training
Education	Kenya Demographic and Health Survey [1]	School attendance Educational attainment
Interpersonal Violence	Kenya Demographic and Health Survey [1] Abuse Assessment Screen [20] Partner Violence Screen [21]	Interpersonal violence prevalence
Mental Health	Patient Health Questionnaire (PHQ-8) [22,23]	Depressive symptom prevalence
Programming	Lwala monitoring and evaluation tools	Service access Service satisfaction
Observational	Kenya Demographic and Health Survey [1]	Mosquito net use Handwashing facility Latrine type
COVID-19	WHO COVID Survey Tool and Guidance [24] van Rie Stigma Scale (adapted) [17–19]	Personal COVID-19 experience Prevention behaviors Testing and vaccination perceptions COVID-19 stigma

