### Participant recruitment and enrollment procedures

Upon arrival to a selected household, the enumerator will first ask to speak to the head of the household. If the head of household is present, the enumerator will then ask if they have children under 5 years old living in the household. If no head of household is present, the enumerator will skip this house, going to the next household along the line selected. They will return to the household later if the head of household is returning home. We define a household as a group of people that eat under the same roof that have lived in the same dwelling for the past year. This excludes temporary visitors.

Heads of households that are 18 years of age or older will be surveyed. Female heads of household are preferred as female family planning, interpersonal violence, and child health and nutrition are key survey areas. Male heads of household will only be surveyed if female heads are unavailable. The only other inclusion criteria will be living in a household in one of the surveyed communities. Households with children under five years of age will be oversampled. Participants will receive 50 KES (about $0.50) in airtime for their participation.

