### Data analysis

After administration, data will be exported to the latest version of Stata (StataCorp LP, College Station, TX) for further analysis. Initial analyses will focus on descriptive statistics of health, socioeconomic, and education metrics in the sample population across areas. Further analyses will characterize these metrics in terms of demographic variables and compare these metrics to county and national averages using appropriate statistical tests, including chi-squared tests, t-tests, ANOVA, and non-parametric tests. These analyses will be conducted following each survey in 2021, 2024, and 2027.

Analysis of outcome metrics will be conducted using multivariable linear regression, logistic regression, and generalized estimating equations. Specific primary outcomes of interest include under-five mortality, immunization rate, skilled delivery rate, contraceptive prevalence rate, and antenatal care visits. Longitudinal analyses will be performed at the end of the study in 2027 once multiple timepoints are available. Interim longitudinal analyses will also be performed following each survey administration. Trends in outcomes and potential effects of programs will be assessed. This will involve interrupted time series techniques with a segmented regression to asses intervention effects over repeated observations.

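### The five-of-seven quota is filled by households with a living under-five, so an unweighted under-five mortality rate is biased low where the quota binds, and more so where fertility is lower

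*Protocol article*

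**What the plan says.** All references are to the protocol article.

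- **Quota** (Sampling strategy): "At least five of seven surveys administered in each grid square will be administered to households with children under five years". Table 2 repeats the split of five plus two for all eight wards, with 127 clusters each.
- **Stopping rule** (same section): the search for households goes on "If the enumerator reaches the end of the grid cell before surveying both seven total households and five households with a child under five years".
- **Who counts** (Participant recruitment and enrollment procedures): if the head of household is present, "the enumerator will then ask if they have children under 5 years old living in the household". The same section states: "Households with children under five years of age will be oversampled".
- **Outcome** (Data analysis): "Specific primary outcomes of interest include under-five mortality, immunization rate, skilled delivery rate, contraceptive prevalence rate, and antenatal care visits".
- **Source of the outcome** (Survey instrument, Table 3): the household module, under the entry "Birth history (child mortality".
- **Methods named** (Data analysis): "Analysis of outcome metrics will be conducted using multivariable linear regression, logistic regression, and generalized estimating equations".

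The one statement on bias in Sampling strategy concerns the starting point of the walk, not the quota. The Limitations section does not mention the quota.

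**The concern.** The variable that fills the quota is partly decided by the event being measured. Take two households, each with one birth in the last five years. If the child survived, the household qualifies for the five or more child places. If the child died, it competes with all other households without an under-five for at most two places. Where those two places fill early, the second household is passed over more often, and a death is lost from the mortality numerator.

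This differs from ordinary over-representation of child households. Over-representation on a characteristic unrelated to child survival would leave deaths divided by births roughly intact; selection on survival does not.

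The link with fertility matters for the third objective, which is to attribute change to the programme. With fewer births per household, a death more often leaves no living under-five. Contraceptive prevalence is itself a primary outcome. If fertility fell in programme wards, measured mortality could fall there with no true change.

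**Working it through.** **The plan's own figures.** The document gives no mortality estimate under the quota to reproduce. Its sample size does reproduce: 50% against 60%, two-sided 0.05 and 80% power give 388; 388 × 1.6 = 620.8 (621); 621 / 0.7 = 887.1 (887); 8 × 887 = 7,096. That calculation is not in dispute here.

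**Inputs from the document.** Seven interviews per square, at most two without a living under-five; true rates q of 82 per 1,000 (Sample size) and 29.5 per 1,000 (Introduction).

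**Assumed, because not given.** Births per household in five years are Poisson with mean λ. Each birth ends in death independently with probability q. Only births in the five-year window count.

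**Formulas.**

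1. Share of households with a living under-five: p = 1 − exp(−λ(1 − q)).
2. Expected interviews per square without one: E = E[min(2, Binomial(7, 1 − p))].
3. Inclusion of such households relative to child households: r = [E / (1 − p)] / [(7 − E) / p].
4. Under Poisson births, deaths are independent of survivors, so a share 1 − p of deaths lies in households with no living under-five.
5. Unweighted estimate = λq[p + r(1 − p)] / {λq[p + r(1 − p)] + λ(1 − q)}.

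**Worked case, λ = 1.0, q = 0.082.** p = 1 − exp(−0.918) = 0.601; E = 1.812; r = (1.812 / 0.399) / (5.188 / 0.601) = 0.525. About 40% of recent deaths lie in the under-sampled group. Sampled deaths are proportional to 0.082 × (0.601 + 0.525 × 0.399) = 0.0665, and surviving births to 0.918. The estimate is 0.0665 / 0.9845 = 67.5 per 1,000, or −18%.

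| λ | p at q = 82 | Reads, true 82 | Bias | Reads, true 29.5 |
|---|---|---|---|---|
| 0.6 | 0.42 | 50.0 | −39% | 18.3 |
| 0.8 | 0.52 | 60.1 | −27% | 22.0 |
| 1.0 | 0.60 | 67.5 | −18% | 24.7 |
| 1.2 | 0.67 | 72.7 | −11% | 26.5 |
| 1.5 | 0.75 | 77.4 | −6% | 28.1 |
| 2.0 | 0.84 | 80.7 | −2% | 29.1 |

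**Comparisons.** At equal fertility the ratio is nearly preserved: true 82 / 29.5 = 2.78; at λ = 1.0 it reads 67.5 / 24.7 = 2.73. At unequal fertility it is not: two wards both truly at 82, with λ = 1.2 and 0.8, read 72.7 and 60.1, a spurious gap of 12.6 per 1,000.

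**Sensitivity.** A simulation of period life tables from birth histories, with lower to higher birth rates (about 0.5 to 2.25 births per household in five years), gave:

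- five-year window: −52% to −7%;
- the same with faster births after a child death: −39% to −3%;
- the same with fertility and mortality also correlated: −30% to −4%;
- ten-year window, across these settings: −33% to −0.1%.

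No scenario reversed the sign.

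**The case against.** **Weighting would remove it, and weighting belongs in an analysis plan that is not shown.** This stands as a limit. Affected households are under-sampled, not excluded, and inverse-inclusion weights return the true rate by construction. The point is therefore about an unweighted estimate and rests on the criterion and quota that the article fixes, not on its silence about weights. But such weights need counts of households passed over once the two places are full. That is a fieldwork record, and an analysis plan cannot recover counts nobody kept. The article neither describes nor rules out such a record.

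**The size is assumed.** This stands. The document gives neither births per household nor the share with a living under-five. Oversampling to 5/7 (71%) suggests that the natural share is expected to be lower, and the same model gives about −8% at a share of 71%, −18% at 60% and −29% at 50%. That is an inference, not a stated figure. The document also does not confine the mortality period to five years, and a longer window shrinks the bias.

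**Sampling error is larger than the gap.** With an assumed 500 to 900 births per ward and a design effect of 1.6, the standard error of a two-ward difference at 82 per 1,000 is about 16 to 22. That is true for one pair of wards, but chance error averages out over wards and rounds, whereas this error does not.

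**Stronger readings.** A reader might infer that every ward is understated by some fixed percentage; the bias is near zero where the quota rarely binds. A reader might infer that comparisons with county and national averages are invalid; the document does not say how those households were selected. A reader might infer that the 29.5 per 1,000 reported for 2017 is itself too low; the sampling of that survey is not described.

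**Conclusion.** The point holds as a conditional bias. Under the quota and screening question as written, an unweighted under-five mortality rate is pushed downward wherever the quota binds, and further as fertility falls. Confidence is high for the direction and the gradient, and low for any single figure. The range of −39% to −2% at a true 82 per 1,000 rests on Poisson births with a mean of 0.6 to 2.0 per household in five years, independent deaths and a five-year window. The bias is small where about three quarters or more of households have a living under-five, and it shrinks with a longer recall period or faster births after a death. Ratio comparisons at equal fertility are little affected. Levels are affected, as are comparisons between wards or over time where fertility differs or changes.

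**What to change.** For the remaining rounds, do one or both of the following.

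**(a) Count and weight.** Record every household screened, including those passed over once the two additional places are full. For each, note whether a child under five lives there and whether any member had a live birth in the last five years. Weight the mortality estimate by the inverse of the inclusion rate.

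**(b) Widen the quota group.** Define it as households with a living child under five or any live birth to a member in the last five years, whether or not the child survives. Keep the five-plus-two numbers. All births in a five-year window then fall in the same group.

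If (b) is adopted, keep status on the present criterion as a recorded variable and also report mortality on that basis. Study design commits later rounds to an unchanged sampling strategy, and a switch would itself raise measured mortality and could appear as a step in the segmented regression.

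For any round already collected without screening counts, state the downward bias as a limitation and give a sensitivity range over assumed under-five shares. The birth histories of sampled households cannot restore those passed over.

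**Cost.** One or two extra screening items, an ethics amendment, and a sensitive question at the door that may be under-reported, which would bring back part of the bias. Under (b), some quota places would have no living child for the vaccination and nutrition modules. In the Poisson model at 82 per 1,000 and λ = 1.0, households with a birth are 1 − exp(−1) = 0.632 and those with a living under-five 0.601, so about 0.031 / 0.632 = 5%, or some 31 of the 5 × 127 = 635 places per ward. The quota is a minimum, so these can be made up.

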### Survey instrument

The survey tool contains over 300 questions and is based on several different validated tools (Table 3). The full survey is available in the supplemental materials (S1 Appendix). The survey is designed to capture metrics across 13 public health modules in a reproducible manner. The estimated time to complete one interview is 45 minutes.

**Table 3 pone.0256555.t003:** Survey modules, key metrics, and sample sizes.

Survey Section	Question Sources	Key Metrics
Personal Demographics	Kenya Demographic and Health Survey [1]	Age Marital status
Household Information	Kenya Demographic and Health Survey [1]	Household census Birth history (child mortality) Total fertility rate
Economics	Kenya Demographic and Health Survey [1] Poverty Probability Index [13]	Poverty probability Multidimensional poverty index Income
Family Planning	Kenya Demographic and Health Survey [1] Condom Use Self-Efficacy Scale [14]	Contraceptive prevalence rate Unmet need for contraception
Child Health	Kenya Demographic and Health Survey [1]	Antenatal care visits Careseeking for childhood illness
Nutrition	WHO Infant and Young Child Feeding [15] Household Hunger Scale [16]	Ever breastfed Exclusive breastfeeding Minimum acceptable diet Household hunger
Vaccinations	Kenya Demographic and Health Survey [1]	Complete vaccination rate
HIV	Kenya Demographic and Health Survey [1] van Rie Stigma Scale [17–19]	HIV testing rate HIV stigma
Water and Sanitation	Kenya Demographic and Health Survey [1]	Drinking water source Previous sanitation training
Education	Kenya Demographic and Health Survey [1]	School attendance Educational attainment
Interpersonal Violence	Kenya Demographic and Health Survey [1] Abuse Assessment Screen [20] Partner Violence Screen [21]	Interpersonal violence prevalence
Mental Health	Patient Health Questionnaire (PHQ-8) [22,23]	Depressive symptom prevalence
Programming	Lwala monitoring and evaluation tools	Service access Service satisfaction
Observational	Kenya Demographic and Health Survey [1]	Mosquito net use Handwashing facility Latrine type
COVID-19	WHO COVID Survey Tool and Guidance [24] van Rie Stigma Scale (adapted) [17–19]	Personal COVID-19 experience Prevention behaviors Testing and vaccination perceptions COVID-19 stigma

### Participant recruitment and enrollment procedures

Upon arrival to a selected household, the enumerator will first ask to speak to the head of the household. If the head of household is present, the enumerator will then ask if they have children under 5 years old living in the household. If no head of household is present, the enumerator will skip this house, going to the next household along the line selected. They will return to the household later if the head of household is returning home. We define a household as a group of people that eat under the same roof that have lived in the same dwelling for the past year. This excludes temporary visitors.

Heads of households that are 18 years of age or older will be surveyed. Female heads of household are preferred as female family planning, interpersonal violence, and child health and nutrition are key survey areas. Male heads of household will only be surveyed if female heads are unavailable. The only other inclusion criteria will be living in a household in one of the surveyed communities. Households with children under five years of age will be oversampled. Participants will receive 50 KES (about $0.50) in airtime for their participation.

### Ethical considerations

The protocol and study design for our household survey was approved by the Ethics and Scientific Review Committee at AMREF Health Africa on March 29, 2021 (AMREF-ESRC P452/2018) and the Institutional Review Board at Northeastern University on September 21, 2020 (IRB #: 20-09-18). A research permit was obtained through the National Commission for Science, Technology and Innovation in Kenya on February 11, 2021 (NACOSTI/P/21/8776). All study personnel will undergo ethical research training.

### Safety and privacy

Prior to data collection, enumerators will obtain informed consent from each respondent in the form of a signature or thumbprint after reading a standardized script informing the respondent of the survey’s purpose and confidentiality policy. Respondents who cannot read or write will be requested to invite a witness to participate in the consenting process. Potential participants are then encouraged to ask questions about the household survey before signing the consent form. Minors (below age 18) will not be surveyed, and consent will only be obtained from adults. For sensitive survey questions, specifically questions regarding mental health and interpersonal violence, an additional female enumerator will be available if female respondents prefer. Respondents will also be provided a contact number for a mental health counselor if concerns are identified.

Data from survey responses will primarily exist as digital copies. If paper surveys are administered due to technology failure, they will be entered into the electronic tool as soon as possible. Paper surveys will be kept in a locked, secure area. Data will be temporarily stored on individual tablets that are password-protected. Upon completion of the survey, data will be uploaded to a secure, privacy-protected online server. Enumerators are required to sign a form declaring that they will keep information obtained confidential and will undergo privacy training prior to survey administration. Interviews will be conducted in as private a location as available in the setting to avoid breaching respondent privacy during the survey itself.

The survey in 2021 will be conducted in the ongoing context of the COVID-19 pandemic. Standard operating procedures have been established to maximally diminish the risk of transmission and to protect both household participants and enumerators. Enumerators will be trained on transmission and prevention of COVID-19. All enumerators will be tested at the beginning of training, prior to survey implementation, and every two weeks during survey administration using a rapid diagnostic test (RDT). Enumerators will be screened for COVID-19-related symptoms each day [25], and any enumerator with symptoms will be referred for testing. If an enumerator tests positive, the Ministry of Health will be notified according to national guidelines [26]. Data collection teams and participants will be provided with sanitation materials and face masks. At all times, social distancing will be maintained between enumerators and participants. In addition, because most people spend their day outdoors and the survey takes place during daylight, interviews will be conducted primarily in outdoor settings to minimize risk of exposure. Each selected potential participant will be asked a series of COVID-19 exposure and symptom questions before the survey can begin. If there is concern for COVID-19 infection, this respondent will not be surveyed. At the end of the survey period enumerators will also be tested for COVID-19 using an RDT to assure no infection occurred during the survey. Lwala will conduct follow-up response per Ministry of Health guidelines, including notifying potentially exposed respondents.

### Enumerator selection, training, and team composition

Surveys will be administered in the household by trained enumerators who are not regular Lwala staff. All enumerators will be hired from the community. Enumerators will be selected from a pool of college graduates or equivalent experience, with preference given to those with experience in survey administration, Dholuo fluency, and high performance in training.

Prior to survey implementation, the enumerators will participate in a five-day training intended to familiarize them with the survey questions and tablet platform, the methodology for household and respondent selection, and recommendations for dealing with potential challenges in the field. Training will focus on the responsible conduct of research, an understanding of the intent of the survey questions, the appropriate translation options in Dholuo, the appropriate skipping of questions according to survey logic, and the procedure for marking responses based on the question type. Enumerators that show signs that indicate the inability to interact appropriately with interviewees or generally do not perform well will be dismissed before field data collection begins.

Data collection teams will consist of a team leader and two enumerators. The team leader will assist in household identification and survey consent while enumerators are completing surveys with eligible households. An overall survey supervisor will also be present to assist with problems that arise and conduct spot checks by observing surveys.

